## Methods/Design

### Study design

In the current study, percutaneous femoral access is compared to open femoral access. Bilateral femoral access is required in each patient treated with a bifurcated EVAR. Therefore, each patient can serve as his/her own control. Randomization is performed for the caliber of the endovascular device (main device versus contralateral extension) that is introduced within the aorta.

The PiERO trial is designed as a randomized, controlled, nonblinded, multicenter superiority trial with two parallel groups and a primary endpoint of wound infection during the 30 days after surgery. Simple randomization will be performed concerning the diameter of the device component introduced in the artery, with a 1:1 allocation.

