### Sample size calculation

The assumption has been made that a pEVAR is less likely to cause a surgical site infection (SSI) than an EVAR with surgical cutdown to the femoral artery. We estimated the number of patients needed in a superiority trial with an effect size of 90 % and a margin of 10 (alpha 5 %, power 80 %). Assuming an SSI incidence of 6.8 % (Table 1) in an open surgical femoral cutdown and of 0.1 % in pEVAR, where *p*1 = 0.068 and *p*2 = 0.001 and using the equation *n* = 8 × (*p*1(1 − *p*1) + *p*2(1 − *p*2))/(*p*1 − *p*2)^2^ [13], 120 patients are required to reach sufficient evidence and avoid a type 2 error (including a fall-out percentage of 5 %).

**Table 1 Tab1:** Wound complication rates mentioned in various studies

Studies	Surgical cutdown	Percutaneous access	Number of patients	*P* value	Research type
Johanning (2001) [8]	nm	0.2	489	-	retrospective
Nehler (2001) [3]	nm	0	189	-	systematic review
Eisenack (2009) [6]	nm	0	500	-	prospective
Zhong (2011) [7]	7.3	0	236	<0.01	retrospective
RIVM (2014)	6.4	nm	329	-	retrospective
Total:	6.8	0.1	1743		

*nm* not mentioned

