### Statistical analyses

#### Primary study parameter(s)

The occurrence of SSIs in both groups will be compared with a McNemar’s test and proportional hazards regression. Only two measuring points will be defined, but wound complications are expected to emerge also between these measuring points. A Kaplan Meier curve may be used to log incidences according to time. Both groups will be compared using the log rank test.

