#### Secondary study parameter(s)

The number of wound complications in both groups will be compared as mentioned previously.

Patient characteristics will be controlled by multivariate analysis with respect to the duration of operation, left/right differences, preoperative bacterial colonization of the nose and the perineum, diabetes mellitus, body mass index, medication, smoking habits and device failure. Although identical groups are examined, we will be able to identify outliers.

Correlations between factors will be estimated using the Pearson correlation coefficient. Proportions of categorical variables are compared using Chi square and Fisher Exact tests, and means of continuous variables are compared using t tests.

The analysis of the primary endpoint (surgical site infection) will be based on an intention-to-treat principle by proportional hazards regression (visualized by Kaplan-Meier survival curves). Intention-to-treat implies that open access because of failed percutaneous access is not excluded from analysis but remains in the percutaneous group. Reasons why percutaneous access may not be successful are inability to obtain access to the arterial lumen with a needle, rupture of the threads of the Prostar XL™ device/2 Proglide™ devices, necessitating open repair and persistent bleeding despite successful use of the Prostar XL™ device/2 Proglide™ devices. The survival analysis is not affected by patient withdrawals (as they will be censored) provided that dropping out is unrelated to prognosis (Table 4). Other outcomes, such as VAS scores 2 weeks post-randomization, may be missing for patients who withdraw from the trial. We will actively seek out reasons for withdrawal and compare the reasons qualitatively.

**Table 4 Tab4:** Number of included patients in the participating centers

Participating center	Number of included patients
- University Medical Center Groningen	13 patients included
- Isala Hospital Zwolle	19 patients included
- Medical Center Leeuwarden	14 patients included
- Wilhelmina Hospital Assen	8 patients included
- Scheper Hospital Emmen	1 patient included
Total:	55 patients included

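### Three analyses are named for the one primary endpoint with none made decisive, and the one given the intention-to-treat role, proportional hazards regression, most likely yields no finite hazard ratio at the planned infection rates

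*Protocol article*

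**What the plan says.** Under Study design, the protocol article has each patient receive open access in one groin and percutaneous access in the other: "Therefore, each patient can serve as his/her own control".

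Under Primary study parameter(s): "The occurrence of SSIs in both groups will be compared with a McNemar’s test and proportional hazards regression". The same paragraph allows for a Kaplan-Meier curve and adds: "Both groups will be compared using the log rank test".

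The primary endpoint returns under Secondary study parameter(s): "The analysis of the primary endpoint (surgical site infection) will be based on an intention-to-treat principle by proportional hazards regression". There, groins converted to open access after failed percutaneous access stay in the percutaneous group. McNemar's test is not mentioned again.

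The Sample size calculation sets "alpha 5 %, power 80" per cent and uses a formula for two proportions, not a hazard ratio: "Assuming an SSI incidence of 6.8 % (Table 1) in an open surgical femoral cutdown and of 0.1 % in pEVAR". It concludes: "120 patients are required to reach sufficient evidence and avoid a type 2 error (including a fall-out percentage of 5" per cent).

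**The concern.** Two stated choices combine badly.

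First, three procedures serve one primary endpoint without an order or a rule for disagreement. One section puts McNemar first, and the other rests the intention-to-treat analysis on proportional hazards regression. With about eight infections expected in total, the choice of test can settle whether the main claim is called significant.

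Second, the planning assumption is that percutaneous infections almost never occur. A hazard ratio cannot be estimated by ordinary maximum likelihood when one arm has no events, so the effect measure of the intention-to-treat analysis is likely to be missing in the very situation the trial expects.

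In addition, log-rank and proportional hazards regression, as named, make no use of the within-patient pairing on which the design rests. Of the three, only McNemar does so by construction.

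**Working it through.** **Inputs.** From Sample size calculation: p1 = 0.068 (open), p2 = 0.001 (percutaneous), two-proportion formula with multiplier 8, 120 patients including 5 % fall-out. From Study design: one groin per technique in each patient. Assumptions made here: the two groins of a patient are independent, and no groin is censored before the last event.

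**1. The plan's own figure.** n = 8 × (0.068 × 0.932 + 0.001 × 0.999) / 0.067² = 8 × 0.064375 / 0.004489 = 114.7. Dividing by 0.95 gives 120.8. The stated 120 is reproduced to within rounding, and 120 × 0.95 = 114 evaluable pairs.

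**2. Expected events.** Open: 114 × 0.068 = 7.8. Percutaneous: 114 × 0.001 = 0.11.

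**3. Chance of an empty percutaneous arm, (1 − p2)^N.**

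| Percutaneous rate | N = 114 | N = 120 |
|---|---|---|
| 0.1 % (planned) | 89.2 % | 88.7 % |
| 0.2 % (assumed) | 79.6 % | 78.6 % |
| 0.5 % (assumed) | 56.5 % | 54.8 % |
| 0.6 % (assumed) | 50.4 % | 48.6 % |

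The higher rates are shown because converted groins stay in the percutaneous group and may raise its rate. An empty arm remains the likelier outcome up to about six times the planned rate.

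**4. What an empty arm does to the model.** Let θ be the hazard ratio, percutaneous to open. With b open events and none percutaneous, the partial likelihood is the product over events of a_i / (a_i + 114θ), where a_i = 114, 113, … It rises steadily as θ falls to 0, so no finite log hazard ratio maximises it, and the Wald statistic and Wald interval carry no information. Stratifying by patient does not help: the estimate becomes the ratio of discordant pairs, 0/b.

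Two tests from the same model survive. The score test is the log-rank test. The likelihood-ratio statistic is 2 Σ ln[(a_i + 114)/a_i], which is 5.60 (p = 0.018) at four events and 7.02 (p = 0.008) at five.

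**5. P values at b:0 discordant pairs, 114 pairs.** Exact McNemar: 2 × 0.5^b. Uncorrected McNemar: chi-square = b on 1 df. Corrected: (b − 1)²/b. Log-rank: from the risk sets.

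| b:0 | Log-rank | McNemar uncorrected | McNemar corrected | McNemar exact |
|---|---|---|---|---|
| 4:0 | 0.044 | 0.046 | 0.134 | 0.125 |
| 5:0 | 0.024 | 0.025 | 0.074 | 0.0625 |
| 6:0 | 0.013 | 0.014 | 0.041 | 0.031 |

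**6. How often this bites.** Per patient, P(open groin only infected) = 0.068 × 0.999 = 0.0679 and P(percutaneous groin only) = 0.001 × 0.932 = 0.0009. With 114 pairs, P(4:0) = 5.5 % and P(5:0) = 8.9 %, together 14.4 %. Over all outcomes (40,000 simulated trials, uniform event times assumed), log-rank and exact McNemar fall on different sides of 0.05 in 15.6 % of trials, but log-rank and uncorrected McNemar in only about 0.1 %.

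**7. Power at the planning rates.** Exact McNemar: 76.4 % at 114 pairs, 79.6 % at 119, 80.2 % at 120. Uncorrected McNemar: 92.3 % at 114. Log-rank (simulated): 92.0 % at 114.

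**The case against.** The strongest reply is that the trouble is smaller than it looks. The article never says that the model will be read through its Wald test. Log-rank is the score test of the unadjusted model, the likelihood-ratio test works with an empty arm, and uncorrected McNemar agrees with log-rank almost always. A conflict needs a Wald reading, or an exact or corrected McNemar, and the article specifies neither. The McNemar version, a clustered variance and a fallback for zero events are details that a statistical analysis plan could supply. A valid paired test is also already listed.

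Much of this stands. A reader might infer that the proportional hazards analysis fails altogether. It does not: the estimate, standard error, Wald test and interval are lost, but two usable tests remain. A reader might infer that the analyses could point in opposite directions. They cannot at the outcomes shown; they differ only on significant versus not significant. A reader might infer that the article commits to treating the groins as independent. It is silent on clustering, so the fair statement is only that the methods, as named, do not use the pairing.

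Nor should the exact version be presented as the repair of an inflated test. The unconditional two-sided error of uncorrected McNemar at 114 pairs, with independent groins, is 4.7 % when both rates are 6.8 %, 4.5 % at 3.4 % or 2 %, and 1.8 % at 1 % (common rates other than 6.8 % are assumptions). The exact test's error is 2.7 %, 1.7 %, 0.7 % and 0.07 %. Choosing between them is a trade-off.

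What the reply does not remove is what the text does state: three analyses for one endpoint, and an intention-to-treat analysis resting on a model whose effect measure will probably not exist.

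**Conclusion.** The point holds in this form. The article names three analyses for the primary endpoint and does not say which one decides. At its own planning rates, the proportional hazards analysis yields no finite hazard ratio in about 89 % of trials. The figure is 80 % at a percutaneous rate of 0.2 % and 56 % at 0.5 %; both rates are assumptions. Whether the result counts as significant depends on the test read at 4:0 or 5:0 discordant pairs, 14 % of trials at the planning rates, if the exact or corrected McNemar is set against log-rank or uncorrected McNemar.

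The 14 % rests on independence of the two groins within a patient. The 89 % needs only the planned percutaneous rate and independence between patients. An analysis plan not shown could set an order, but the article's two statements would still need to be reconciled with it.

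**What to change.** Name the McNemar test, already listed under Primary study parameter(s), as the single primary analysis, on patient pairs and by allocated technique. Fix its version (exact, corrected or uncorrected) in advance. Report the paired risk difference with a score-type confidence interval, such as Tango's or Newcombe's, which can be computed with an empty arm. Reword the intention-to-treat sentence under Secondary study parameter(s) so that it refers to this test.

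Make Kaplan-Meier, log-rank and proportional hazards regression descriptive or secondary. If a hazard ratio is reported, account for the patient pair and use Firth penalisation or profile likelihood; stratification by patient alone does not cure an empty arm.

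The change is one of wording, with no new data to collect. Table 4 lists 55 included patients, so at that stage the choice could still precede the final analysis. It is not free if the exact version is chosen: power is about 76 % at 114 pairs and reaches 80 % only at about 120 evaluable pairs, which leaves nothing of the 120 for the 5 % fall-out. Either state that power or raise recruitment: 120 / 0.95 = 126.3, so about 127 patients. The uncorrected version keeps about 92 % power at 114 pairs, with unconditional error below 5 % in the cases checked.

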#### Publication of data

The scientific integrity of the project requires that the data from all sites be analyzed study-wide and reported as such. Thus, an individual center is not expected to report the data collected from its center alone. All presentations and publications are expected to protect the integrity of the major objectives of the study.

Recommendations will be given by Abbott, and Abbott will be granted the nonexclusive right to use any publication or presentation resulting from the research.

Publications will be prepared under the responsibility of the principle investigator and the contributions of all authors will be specified. A copy of such publication will be provided to Abbott for its review and comment. The principle investigator will give due consideration to any comments made by Abbott. Changes will be incorporated only when Abbott will require protection of Abbott’s proprietary rights and interests. This will not interfere with the ethical responsibility to disseminate the trial results in an unbiased and timely manner; consequently, Abbott cannot prohibit publication.

## Discussion

Comparison of the incidence of SSIs in one patient may answer (an important part of) the question whether percutaneous closure devices deserve a role in the prevention of SSIs after EVAR. The cost of an SSI is estimated to be between US $10.000, and $20.000 per infection [19]. In pEVAR, a trend was noticed to reduce procedure and hospitalization times [10–12, 20]. The aim of this study is to contribute to the rationale of using percutaneous devices for femoral access in EVAR.

Analysis will be performed on an intention-to-treat basis. When a percutaneous access, for some reason, is not successful, open access will be obtained. Reasons why percutaneous access may not be successful are described in the Statistical Analysis section.

For all participants, cultures of the nose and the perineum will be taken preoperatively. In addition, two punch biopsies from the right groin will be obtained to evaluate the presence of microorganisms in deeper layers of the skin or intracellularly (by culture/molecular methods and PA research). The intention is to compare cultures and SSIs as it becomes more apparent that differences in hostility between bacterial species and/or clones exists [16, 17]. Therefore, the assumption was made, that a SSI does not only develop due to flaws in sterility [21], but also because some bacteria might be able to conceal themselves better in or on their host, than other bacteria. We know that bacteria can hide intracellularly [17, 22], and take over resistance genes from each other. Therefore, it might be interesting to compare *S. aureus* strains not causing SSIs, to those that do cause an SSI.

In conclusion, the PiERO trial is a multicenter randomized controlled clinical trial designed to show the consequences of using percutaneous access in EVAR surgery, when considering surgical site infections. In addition, patient comfort, estimated hospital stay and other wound complications are taken under consideration.

## Trial status

Patients have been included as follows in the various participating centers:

## Abbreviations

AE: adverse event
CERTE: the name of the infectious laboratory
CFA: common femoral artery
CMO: Commissie Mensgebonden Onderzoek = Commission Research on Humans
CRF: case report form
EVAR: endo-vascular aneurysm repair
FISH: fluorescence in situ hybridization
Fr.: French
Nm: Not mentioned
pEVAR: percutaneous endovascular aneurysm repair
PiERO: Percutaneous access in Endovascular Repair versus Open access
SAE: serious adverse event
SSI: surgical site infection
SWA-score: Southampton Wound Assessment score
VAS: Visual Analog Scale
